### 2.8. Initial Assessments

Initially, demographic and past medical history details (age, height, body mass, medical history, previous illnesses, concomitant diseases, use of medications, prior surgeries, physio therapeutic treatment, professional occupation and other aspects) will be collected, and a series of special tests will be administered by a physiotherapist, who will be blinded to participants’ subsequent group allocation. A physiotherapist with a Master of Science in Advanced Physiotherapy and at least six years of experience in clinical practice will evaluate the assessment of all outcomes. The planned sequence of outcome assessments is depicted in Figure 3. 

### 2.9. Outcomes

The evaluations will take place at all time-points: before the treatment sessions (week 0), after ten treatment sessions (week 4), and four months after the beginning of the trial (week 16). The primary outcomes will be: functional disability (NDI) [25] and pain (VAS) [26]. Several secondary outcomes will also be evaluated: cervical range of motion (CROM) [27], craniovertebral angle (CVA) [28], Nijmegen Questionnaire (NQ) [29,30], Hi-Lo test [31], breath holding time (BHT) [32,33], single breath count (SBC) [34], end tidal CO_2_ (ETCO_2_) [35] and respiratory rate (RR) [36], chest wall expansion (CWE) [37], the Hospital and Anxiety Depression Scale (HADS) [38], the Tampa Scale for Kinesiophobia (TSK) [39] and adverse events [40]. All outcomes are briefly presented below. The corresponding references for each of the above outcomes include reliability and validity details, except for some further testing proposed in Section 2.10 and Section 2.11.

#### 2.9.1. Primary Outcome Measures

The Neck Disability Index (NDI) [25]: The NDI is a disability self-report tool in relation to neck pain. It consists of 10 questions, with 6 alternative responses each, that relate to the ease of performing different tasks, pain severity, and the coexistence of headache. Each item’s score ranges from 0 (no pain and no functional limitation) to 5 (worst pain and maximum limitation), for a total score that ranges from 0 (no disability) to 50 (totally disabled).

Pain Intensity-Visual Analog Scale (VAS) [26]: Subjective pain intensity registration, by the selection of a value between 0 (no pain) and 100 (maximal pain) that best describes the intensity of pain felt in the last 24 h.

#### 2.9.2. Secondary Outcome Measures

Range of motion (ROM) [27]: A smartphone-based application (iHandy Level: https://play.google.com/store/apps/details?id=com.ihandysoft.carpenter.level.free&hl=et&gl=US (accessed on 10 May 2022)) downloaded to a smartphone (Model P30/ELE-L29, Huawei Smartphone, China 2019, purchased January 2021), in parallel with a sensor-based commercially available device (KFORCE SENS electronic goniometer, KINVENT-France), will be used to accurately measure ROM during neck movements of flexion-extension, left-right side flexion, and left-right rotation. 

Craniovertebral Angle (CVA) [28]: Lateral photography examination of the FHP through lateral photographs can provide very reliable estimates. FHP will be estimated in a relaxed sitting position for all participants. A smartphone-based application (Forward Head Posture-FHP app), available on Google Play (https://play.google.com/store/apps/details?id=com.ysjworld.fhp&hl=en&gl=US (accessed on 10 May 2022)), will be used for CVA angle measurements.

Nijmegen Questionnaire (NQ) (Greek version 2014) [29]: Screening tool used to detect patients with hyperventilation complaints and DB patterns. Scores > 19 are used as the cut-off score to separate hyperventilatory patients from normal subjects [30]. NQ values in healthy individuals range from 10 to 12 ± 7, and values have been observed to decrease towards these levels in subjects with DB after breathing retraining [30].

Hi-Lo test [31]: The examiner will be given instructions on how to conduct and record results from the Hi-Lo test, including the following: “Examiner at the front and slightly to the side of the individual has to place one hand on the patient’s sternum and the other hand on their upper belly. The examiner must evaluate if and to what extent abdominal or thoracic motion predominates while breathing. Additionally, paradoxical breathing needs to be considered, as well as the degree of abdominal or thoracic breathing rate.” This test evaluates DB.

Breath Holding Time (BHT) [32]: This test is an indicator of a person’s respiratory response to biochemical, biomechanical, and psychological factors, and it seems that abnormally shortened BHT may indicate abnormalities in respiratory function that are closely related to DB. Participants will be instructed to assume a comfortable sitting position and breathe normally and gently, in and out, and at the end of a normal exhalation, they will be asked to pinch their nose and hold their breath. The instruction is to hold their breath to the point when they cannot hold their breath any longer and are required to breathe in again. According to Kiesel (2020) [33], a BHT < 25 s is considered as a sign of DB.

Single Breath Count (SBC) [34]: Participants will be requested to count out loud after maximal inspiration. The ability to reach a count of 50 (corresponding to 25”) is considered as normal respiratory function. This test evaluates DB.

End-Tidal CO_2_ (ETCO_2_) [35] and Respiratory Rate (RR) [36]: These outcomes are measured by a standard capnograph unit. An ETCO_2_ average value that is less than 35 mm Hg over a 12 min period and an average RR of more than 16 breaths/min, will be considered as signs of DB.

Chest Wall Expansion (CWE) [37]: A tape measure will be used to determine the difference between the readings of thoracic cage circumference acquired during deep inspiration and expiration, with higher values indicating a better result.

Hospital and Anxiety Depression Scale (HADS) (Greek version 2008) [38]: Anxiety and depression are measured by the anxiety and depression level assessment scale commonly used in musculoskeletal research, with 7 items contained in each of the subscales (range of scores between 0–21 for each), assessing the two constructs. For each of the two subscales, a score of >8 denotes clinically relevant anxiety/depression.

Tampa Scale for Kinesiophobia (TSK) (Greek version 2005) [39]: Kinesiophobia is a frequently utilized psychological measurement of pain-related fear in musculoskeletal clinical conditions. The translated version of the original 17-item questionnaire will be used.

Adverse events [40]: Potential adverse effects of therapy will be evaluated during and after the physiotherapy treatment, according to a proposed 5-level rating. Should any patient present with serious adverse events, they will be withdrawn from the trial and referred back to their doctor for further evaluation.

The order of administration of the outcome assessments is presented in Figure 3. Any reactive or interactive effects of the measurements [21] conducted sequentially may not be avoided; however, these effects are expected to affect participants allocated in either of the treatment groups in the same manner. All outcomes will be accumulated for statistical analysis, which will be conducted by a professional statistician.

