### 2.7. Participants’ Characteristics

At least 90 adult volunteers of both genders, aged between 25 and 65 years, and with mechanical chronic neck pain (for more than 12 weeks), Grade I or II according to the Task Force on Neck Pain classification (Nordin 2009) [22], negative Spurling’s test, traction test, upper limb tension test, and shoulder abduction test, understanding and fluently speaking the Greek language, and the absence of another serious pathology, will be included in the present study. The diagnosis of non-specific mechanical chronic neck pain will be performed after history taking and physical examination (according to the clinical protocols of IFOMPT) [23] and medical X-rays, according to the Canadian Cervical Spine Rule (C-Spine) and the National Emergency X-Radiography Utilization Study (NEXUS) [24]. Patients will also be selected on the basis of demonstrating DB in at least one of a series of tests conducted to assess the extent of their DB (biomechanical, biochemical, psychological).

The following criteria will be used to determine who is excluded: history of cervical trauma, whiplash injury, or cervical surgery; cervical hernia; spinal degenerative disease; upper limb pain radiation; having received physiotherapeutic treatment for the cervical region within the previous three months; metabolic bone diseases and osteoporosis; cardiac or respiratory insufficiency; pregnancy; neoplasm; infectious diseases; psychological diseases; red flags (overnight pain, serious muscle spasm, weight-loss unrelated to diet, daily headache, dyspnea, confusion, and loss of consciousness); recent consumption of analgesics, anti-inflammatories, or muscle relaxants; systemic illnesses; and fibromyalgia.

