#### 2.10.3. Prevalence of DB in Patients with NSCNP

As there are no established reference standards for DB [33], the diagnostic accuracy of respiratory measurements relating to DB in patients with NSCNP cannot be examined. Instead, as previously proposed [42], the prevalence of DB in patients with NSCNP can be presented, using cut-off scores established from previous studies performed in an asymptomatic population without a respiratory condition (ETCO_2_ with a cut-off score of 35 mm Hg, the NQ with a cut-off score of 19), and the Hi-Lo test, for the determination of the type of breathing, as single or combined (in pairs, or using all three) outcomes, to identify the percentage of the population with NSCNP that exhibits respiratory dysfunction. 

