## 3. Discussion

Previous research has investigated many interventions and outcomes for the amelioration of symptoms in NSCNP; however, until now, many patients have reached a plateau in their rehabilitation, without full resolution of their symptoms [6,7]. One explanation for this partially successful approach is that patients with NSCNP present not only musculoskeletal, but also respiratory disorders, both contributing to the symptomatology of chronic neck pain [8,9,10]. 

The present study’s innovative approach resides in its emphasis the importance of recognizing all components of breathing dysfunction. DB is multi-dimensional and contains biochemical, biomechanical, and psychophysiological components [33,42]. The present study surmises that no single test or questionnaire can identify breathing dysfunction; therefore, a battery of tests is proposed for the identification of breathing dysfunction [30,31,32,33,34,35,36]. As a result, additional validity investigations and interventions are required in patients with NSCNP in order to cover additional aspects of their pathology.

The study aspires to provide a more holistic approach in patients with a condition which has, up until now, been considered to involve mainly the neuromusculoskeletal system [18,19]. The specific components of this approach have not yet been determined. It is possible that the release of the diaphragm, in combination with breathing reeducation, will not only decrease pain and other musculoskeletal-related outcomes, but also may improve the body’s ability to achieve homeostasis, in general [19]. 

There are certain limitations in the study that must be taken into account. The physiotherapist in charge of carrying out the treatment cannot be blinded, due to the nature of the proposed therapeutic procedures. The intervention’s length, frequency, and number of sessions is similar to the one generally provided in current practice, although it may be that longer-term interventions or a different components’ combination can be even more effective. Finally, no true control group will be included; instead an active control (conventional physiotherapy, CP) group is selected for ethical reasons, as well as for blinding purposes, as in this manner, all patients will receive an active treatment for their conditions [21]. 

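### Section 2.10.3 reads a Nijmegen score above 19 as respiratory dysfunction with no background rate, although the plan's own healthy values put roughly 9-16% of healthy people above that cut-off

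*Protocol article*

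**What the plan says.** Four places in the protocol article bear on this.

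- **Section 2.9.2 (Secondary Outcome Measures)** gives both the healthy NQ values and the rule for abnormality: "NQ values in healthy individuals range from 10 to 12 ± 7", and "Scores > 19 are used as the cut-off score to separate hyperventilatory patients from normal subjects". It calls the NQ a screening tool.
- **Section 2.10.3 (Prevalence of DB)** concedes that DB has no established reference standard, so diagnostic accuracy cannot be studied. It proposes a prevalence instead, from end-tidal CO2 (cut-off 35 mm Hg), "the NQ with a cut-off score of 19", and the Hi-Lo test. The results are to be used "as single or combined (in pairs, or using all three) outcomes, to identify the percentage of the population with NSCNP that exhibits respiratory dysfunction". No expected rate in healthy people and no healthy comparison group is described.
- **Section 2.7 (Participants' Characteristics)** restricts entry: "Patients will also be selected on the basis of demonstrating DB in at least one of a series of tests", covering biomechanical, biochemical and psychological aspects.
- **Section 3 (Discussion)** takes the position that "no single test or questionnaire can identify breathing dysfunction", and proposes a battery of tests for that reason.

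**The concern.** A cut-off about one SD above the healthy mean will be exceeded by a noticeable minority of people whose scores are entirely ordinary. If the proportion above it is reported as the percentage with respiratory dysfunction, some positive percentage will appear even if neck-pain patients score exactly as healthy people do. A reader cannot tell how much of the figure is excess and how much is background.

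This matters because respiratory involvement in chronic neck pain is the rationale for the experimental treatment. A prevalence from this study would naturally be cited as support for that rationale. The single-test reading also sits badly with the plan's own statement that one test is not enough.

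**Working it through.** The protocol states no specificity or background rate for the NQ, so there is no figure of its own to reproduce. The check uses its healthy values.

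**Inputs**
- Healthy mean 10 to 12, spread 7 (section 2.9.2). The text does not label ±7; reading it as an SD is an assumption.
- Positive if the score is above 19 (section 2.9.2). Section 2.10.3 says only that the cut-off is 19.
- Planned sample of at least 90 (section 2.7).

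**Step 1. Share of healthy people above the cut-off.** With roughly normal scores the share is 1 − Φ((c − mean)/7).

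| Healthy mean | c = 19 | c = 19.5 (integer score of 20 or more) |
|---|---|---|
| 10 | z = 9/7 = 1.29, 9.9% | z = 9.5/7 = 1.36, 8.7% |
| 11 | z = 8/7 = 1.14, 12.7% | z = 8.5/7 = 1.21, 11.2% |
| 12 | z = 7/7 = 1.00, 15.9% | z = 7.5/7 = 1.07, 14.2% |

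**Step 2. Does it depend on normality?** Right-skewed distributions (gamma, lognormal, negative binomial) with the same mean and SD give about 8.5% to 14.9%. If a score of exactly 19 also counted as positive, c = 18.5 gives 11.2% to 17.7%. The order of magnitude does not change.

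**Step 3. In people.** In 90 unselected people with healthy NQ scores, 90 × 0.087 = 7.8 to 90 × 0.159 = 14.3, so about 8 to 14, would be NQ-positive.

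**Step 4. Why Step 3 cannot be applied to the enrolled 90.** Section 2.7 admits only people with at least one positive DB test. It does not name the tests. Sections 2.9.2 and 2.10.2 treat the NQ as a DB measure, so it is presumably one of them. Every NQ-positive person then passes this criterion. If p is the NQ-positive share among all assessed and A is the share of them with at least one positive test, the NQ-positive share among those admitted is p/A. The protocol does not give A. Any A below 1 raises the figure. Purely as an illustration, letting A run from 1 down to one half takes 8.7-15.9% up to as much as 17.4-31.8% with no excess in breathing problems at all. The enrolled sample therefore cannot yield a population prevalence.

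**Step 5. Combined results.** If combined means that every test in the set is positive, the share positive on a pair or triple cannot exceed the share positive on any one of its tests, and will usually be well below it. The background problem is smaller there. The documents give no healthy rates for end-tidal CO2 or Hi-Lo, so it cannot be quantified further.

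**The case against.** The other side has substantial points, and most of them stand.

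- **Section 2.10.3 is candid.** It says that there is no reference standard, drops accuracy, and reports pairs and all three tests as well as single tests. The combined results are a real safeguard. What remains is that single-test results are still given the same label of dysfunction.
- **These are not false positives.** A reader might infer that such a prevalence could consist wholly of false positives. The documents do not support that: without a reference standard, a healthy person scoring above 19 cannot be said to be free of DB. What follows is a background positive rate.
- **The entry rule is defensible.** A reader might infer that admission on one positive test contradicts the Discussion and fills the trial with chance positives. The Discussion goes on to propose a battery because DB has several dimensions, and an at-least-one rule across a battery is a coherent, sensitive entry rule. How many entrants would qualify by chance cannot be calculated, because section 2.7 does not list the tests and healthy values are given only for the NQ.
- **The trial's main result is untouched.** Entry is settled before allocation, so the comparison of the groups on the Neck Disability Index and pain is not biased. Prevalence is not among the four numbered objectives in the Introduction, and section 2.10.3 says only that it can be presented.
- **±7 is not labelled and normality is assumed.** True, but Step 2 shows that the conclusion does not depend on the shape of the distribution.

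**Conclusion.** The point holds for how single-test prevalence is estimated and read in section 2.10.3, and no further. On the plan's own healthy values, about 9-16% of healthy people would exceed the NQ cut-off (8.7-14.2% for an integer score above 19), provided that ±7 is an SD. A single-test percentage reported without that background overstates what it shows, and taking it from enrolled patients would inflate it again through the entry rule.

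It would be tempting to go further and set a count among the 90 enrolled patients above which dysfunction is declared. That would not work: those patients are selected on having a positive test, so a threshold built on the unselected background rate could be passed through selection alone. Nor is there ground for changing the entry rule or adding a subgroup analysis of treatment effect by number of positive tests; that would be a low-powered preference, not a correction.

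**What to change.** In section 2.10.3:

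1. Calculate prevalence in all assessed patients with non-specific chronic neck pain, before the criterion of at least one positive DB test is applied. That criterion already requires the tests to be done at the initial assessment.
2. Give the NQ single-test prevalence with its 95% confidence interval beside the expected healthy rate of about 9-16%, state the SD assumption, and claim an excess only if the interval lies above that rate.
3. Call single-test results 'screen positive', and rest any statement about dysfunction on the combined results, saying that combined means jointly positive.
4. If only enrolled patients are available, state that the single-test figures are inflated by selection and make no population prevalence claim.

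The cost is wording, plus keeping the initial test results of people who are assessed but not enrolled, which their consent should cover. No new measurement is needed. The downside is a less favourable prevalence statement.

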### 2.10. Respiratory Outcomes Validity Investigation in Patients with NSCNP

#### 2.10.1. Construct Validity of the NQ 

The assessment of the construct validity of the NQ will be performed via exploratory factor analysis, similar to its previous validation in a population with asthma [29], to examine the factor structure of the NQ in a population with NSCNP. This study has not been performed in a population with chronic pain and without a respiratory condition, such as the one under study.

#### 2.10.2. Concurrent Validity of Respiratory Outcomes Assessing DB

The examination of relationships between the following respiratory outcomes of DB (concurrent validity) will be performed: the NQ (psychophysiological dimension), ETCO_2_ (biochemical dimension), and RR, Hi-Lo, BHT, SBC, CVA, CWE (biomechanical dimension). Similar research has previously been conducted [41], but not in a population with NSCNP.

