### Objectives of the Proposed Study

Based on these findings and the hypotheses underlying the observed respiratory and psychological dysfunction in patients with NSCNP, the aims of this study will be to assess: (1) the effectiveness of manual therapy in the cervical spine (CMT) and diaphragm (DMT), in combination with breathing reeducation exercises (BREx), on musculoskeletal and respiratory outcomes in patients with NSCNP, and (2) the effectiveness of CMT alone or conventional physiotherapy (CP) on respiratory outcomes. Additionally, two additional objectives relating to the initial development of the outcome measures used in this study will be to examine: (3) the construct and concurrent validity of specific respiratory outcomes relating to DB in patients with NSCNP, and (4) the reliability of biomechanical-based assessments.

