### 2.15. Statistical Analysis

Baseline characteristics and all outcome measurements will be analyzed initially in each group for normality of their distribution using the Shapiro–Wilk Test. Descriptive statistics will be used to present the distribution of the data.

Statistical analysis for the RCT will be conducted, based on intention-to-treat analysis. In this way, the individuals will be analyzed in the groups in which they were randomly allocated. A separate analysis will be conducted in case any protocol deviations occur for part of the population, such as low adherence with the organized treatment sessions, low home compliance (<50% attendance), or should patients withdraw themselves from the RCT. Linear mixed models (two-way mixed ANOVA) with one repeated measures factor (time) and another between-groups factor (group), especially considering the interaction between the factors of time (week 0, week 4, and week 16) and group (A and B, A and C, B and C). Additionally, post hoc tests will be employed to determine the source of the interaction, if significant. 

The principal components analysis method will be performed for the factor analysis of the NQ. Pearson’s bivariate correlations will be employed for the examination of concurrent validity of respiratory outcomes.

For all analyses, a significance level of 5% will be considered. All data processing will be performed using the IBM SPSS software, version 28. 

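### Objective 3 and section 2.10.2 promise concurrent validity for eight breathing measures without a criterion, so the planned correlations can support at most convergent validity, and the stated 5% level cannot establish even that

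*Protocol article*

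**What the plan says.** The third objective (Objectives of the Proposed Study) is to examine "the construct and concurrent validity of specific respiratory outcomes relating to DB in patients with NSCNP". Section 2.10.2 carries this out for concurrent validity: "The examination of relationships between the following respiratory outcomes of DB (concurrent validity) will be performed". The measures are NQ for the psychophysiological dimension, ETCO2 for the biochemical dimension, "and RR, Hi-Lo, BHT, SBC, CVA, CWE (biomechanical dimension"). No measure in this list is designated as the criterion.

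Section 2.15 gives the method: "Pearson’s bivariate correlations will be employed for the examination of concurrent validity of respiratory outcomes". It closes with a general rule: "For all analyses, a significance level of 5% will be considered".

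Section 2.10.3 opens with "As there are no established reference standards for DB" and for that reason rules out a study of diagnostic accuracy. The Discussion adds that "DB is multi-dimensional and contains biochemical, biomechanical, and psychophysiological components", and argues that a battery is needed because no single test or questionnaire can identify the condition.

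**The concern.** Concurrent validity means agreement of a measure with an accepted criterion taken at the same time. The article says that no such standard exists for DB, names none among the eight measures, and argues in the Discussion that no single test could serve. The label on Objective 3 therefore conflicts with the article's own premises. Correlations among imperfect measures of a many-sided construct can show convergence, which is evidence of construct validity and is judged against expectations about direction and size.

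The stated method does not fill that gap. A significance test of a Pearson correlation asks whether r differs from zero. It does not ask whether two measures are related closely enough, or in the expected direction, to support a validity statement. At stake is what Objective 3 can conclude, and how a reader would understand a report that these measures have concurrent validity in patients with non-specific chronic neck pain.

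**Working it through.** **Plan's own figure.** The article states no sample size, threshold or precision for the correlation analysis, so there is none to reproduce. The trial's sample size (section 2.14) is a minimum of 80, raised for 10% dropout: 80 / 0.90 = 88.9, so 89, rounded up to 3 × 30 = 90. That step reproduces. The 80 itself cannot be verified, because the assumed correlation between repeated measures, the non-sphericity correction and the effect-size option are not given. Nothing below depends on how it was derived.

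**Inputs.**
- Measures: NQ, ETCO2, RR, Hi-Lo, BHT, SBC, CVA, CWE = 8 (section 2.10.2).
- Patients: 90 (section 2.7, at least 90) or 80 (section 2.14). Use of baseline data is an assumption, as the article does not say which visit is used.
- Level: 5% (section 2.15). Two-sided testing is an assumption, as sidedness is not stated.
- No adjustment for multiple correlations is stated.

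**Step 1: the smallest correlation that reaches significance.** The critical value is |r| = t / sqrt(t² + n − 2), with t the 97.5% point on n − 2 degrees of freedom.
- n = 90: t = 1.987, so |r| = 1.987 / sqrt(3.949 + 88) = 0.207 and r² = 4.3%.
- n = 80: t = 1.991, so |r| = 1.991 / sqrt(3.963 + 78) = 0.220 and r² = 4.8%.

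**Step 2: precision at that point.** The Fisher-z interval is tanh(atanh(r) ± 1.96 / sqrt(n − 3)). For r = 0.21 and n = 90 it is tanh(0.213 ± 0.210), or about 0.003 to 0.40. A just-significant result is therefore compatible with almost no relationship and with a moderate one.

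**Step 3: number of tests.** Pairs = 8 × 7 / 2 = 28. If all are tested and every true correlation is zero:
- expected significant results = 28 × 0.05 = 1.4;
- chance of at least one, treating the tests as independent = 1 − 0.95^28 = 0.762. A simulation of eight independent normal variables (n = 90, 20,000 runs) gave 76.3%.

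**Step 4: would a multiplicity correction be enough?** Bonferroni over 28 pairs (0.05 / 28) moves the cut-off at n = 90 only to |r| = 0.325, or 10.6% shared variance. The false-positive count falls, but the question is still whether r = 0.

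**Step 5: the texts together.** Section 2.10.2 claims a criterion-based property. Section 2.10.3 says that no standard exists, and the Discussion says that no single test can identify DB. These fit together only if the claim in section 2.10.2 and Objective 3 is reduced to convergence among measures.

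**The case against.** The strongest reply is that this is a matter of vocabulary. Both the objective and section 2.10.2 speak of examining relationships. Section 2.10.3 uses the missing standard to rule out diagnostic accuracy, not correlation, and the computation would be the same under either name. Expected values, thresholds and multiplicity rules may also sit in a full protocol or analysis plan that is not shown. Much of this stands: the absence of numerical expectations from an article is not itself a fault. But no further document can supply a criterion that the article says does not exist, and the name determines what may be concluded.

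A reader might infer several stronger points that the article does not support:
- **That any significant correlation will count as validity.** No text says so. The 5% line covers all analyses and is not presented as an acceptance rule for validity.
- **That no result could count against validity.** A null or wrong-direction correlation could. The article simply names no such result.
- **That an unsound validity claim would carry into the trial results.** The primary outcomes are NDI and VAS (section 2.9), and no randomised comparison is conditional on section 2.10.2. Section 2.11 does make some outcomes conditional, but on reliability.
- **That CVA does not belong in the set.** The Introduction links forward head posture with altered breathing, and a correlation needs no cut-off. CWE has none either.
- **That correlations must be lower across dimensions than within them.** The Introduction expects respiratory rate to fall as end-tidal CO2 rises, and section 2.9.2 describes BHT as reflecting all three kinds of factor.

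The chance figures in step 3 also assume that every true correlation is zero, which the article's rationale makes unlikely. They show what the 5% level permits and do not forecast the result.

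**Conclusion.** The point holds as a mismatch between label, premise and method. Objective 3 and section 2.10.2 promise concurrent validity, but there is no criterion, so the correlations can support at most convergent validity. The one stated criterion is met at |r| of about 0.21 to 0.22 with 90 to 80 patients. Such a correlation is weak, and too weak to carry a validity conclusion alone. These values assume baseline data and two-sided tests; the chance count of 1.4 further assumes that all 28 pairs are tested with no true association. The consequence is limited to what Objective 3 may conclude. The change is worth making before analysis, because expectations about the correlations have force only if they are fixed in advance.

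**What to change.** 1. Rename section 2.10.2 and the matching part of Objective 3 as convergent validity.
2. Before analysis, record the expected direction and approximate size of each correlation to be examined. The investigators should choose the values from the trial's own rationale. One common bar for all pairs is not advisable: the article offers no basis for a value such as 0.5, and if the whole 95% CI had to exceed 0.5 at n = 90, the observed r would need to reach tanh(0.549 + 0.210) = 0.64.
3. Report each r with its 95% CI and the share of expectations met.
4. State that no validity conclusion will be drawn from p < 0.05 alone.

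The cost is wording and a short table of expectations; no new data are needed. The downside is that fewer measures may be called valid.
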